#### Electronic record review (objectives 3 and 4)

Medical record-keeping systems in Anhui province will be described in detail using information from clinic observations and consultations with clinical personnel and medical centre directors. Outpatient electronic care systems will be interrogated 2 weeks or more after patient recruitment and compared with notes from clinic observations to assess completeness and accuracy of electronic care records. A 1-year sample of all electronic care records from the participating facilities will then be drawn to investigate patterns and rates of antibiotic prescribing in relation to recorded diagnosis, clinical indication and laboratory results.

### Structured exit surveys (objectives 5 and 6)

Exit surveys will be carried out with patients presenting with symptoms of sore throat, RTI or UTI following either their consultation at a healthcare facility or their visit to a retail pharmacy. Those who consent to being recruited will complete the survey prior to leaving the facility. Using a brief semistructured questionnaire developed from open-ended interview responses in the study’s pilot phase, the survey will solicit details of symptoms, perception of the problem (lay diagnosis), professional and/or self-treatment taken before the visit, whether the diagnosis and treatment received (including prescribed antibiotics) is as expected, as well as views on specimen collection and microbiological testing in patients attending the healthcare facility.

#### Semistructured observations (objectives 3, 5 and 6)

These will occur at all the participating clinics, health centres and retail pharmacies. At clinics and health centres, the observation focuses on daily operational routine including test ordering, prescribing, patient recall and other standard procedures using a predesigned worksheet, together with observational notes on clinical encounters. At retail pharmacies, the observation uses a similar worksheet and documents daily encounters between customers and shop assistants including the health problems presented, and medicines and information asked for by the customers and/or suggestions made and medicines and information given by the assistants.

#### In-depth interviews (objectives 5 and 6)

These will involve a subsample of the patients (previous experience of similar studies suggests that around 60 in total are likely to be needed to reach data saturation) and customers (around 60) who have completed the exit survey and all the related doctors and salespersons who have served the participating patients or costumers. Interviews with individual patients and customers will be undertaken, respectively, at their homes and at the pharmacy 1–2 weeks after their initial visit; interviews with individual doctors and salespersons will take place any time during the study period when they are free. Topic guides refined during the pilot phase of the study will be used to focus patient interviews on the illness episode for which treatment was sought and any previous action taken to manage the illness, while interviews with doctors focus on the following main topics: professional experience and expertise, normal practice, prescribing antibiotics, patient influences on antibiotic prescribing and external influences on antibiotic prescribing.

A subsample of interviewees will take part in pile sorts, a qualitative method in which informants are provided with a set of index cards each showing a pertinent term and asked to group the cards according to their perceived appropriate clustering of terms. Terms will be antibiotics-related and derived from earlier exit surveys, observations and in-depth interviews.^31 32^ This method provides another means to distinguish how informants understand antibiotics and their use.

### Data analysis

#### Quantitative analysis (objectives 1–4)

Data from the microbiological testing, review of clinical records and exit surveys will be analysed quantitatively to investigate prevalence of infection and rates of resistance, relationships between infection/resistance rates and patient characteristics and feasibility of routine microbiological testing in rural clinics. The feasibility of obtaining community-based samples of common pathogens and determining their antibiotic sensitivities (objective 1) will be examined by: (1) ratios of patients who have provided specimens versus those who have refused and their reasons for doing so; (2) percentages of specimens assessed as being properly collected, preserved and shipped by designated microbiological technicians; (3) ratios of positive versus negative attitudes toward giving specimens among the exit interviewees and views of the participating doctors. Prevalence of pathogens and AMR (objective 2) will be assessed by: (1) estimating percentages of pathogen positive specimens in terms of all and specific bacteria by diagnosis, type of specimen, patient-reported symptoms, previous treatment history and sociodemographics; (2) calculating percentages of resistant pathogens by type of bacteria and antibiotics and (3) comparing, using χ² test, these pathogen and resistance rates in non-hospitalised patients with those from analyses of data from large urban hospitals. We will produce a descriptive analysis of patient record systems and electronic record completeness and accuracy (objective 3). If sample sizes allow it, descriptive analyses may be followed by analytical studies to explore relationships between pathogen types and susceptibilities and patient characteristics such as presenting symptoms, clinical diagnosis, prior use of antibiotics and demographics (objective 4).

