### Participants

The microbiological substudy aims to recruit a total of 1550 patients (1000 with exacerbation of chronic obstructive pulmonary disease (COPD) and 555 with UTI). We estimate that this will yield 200 *Escherichia coli* isolates and 100 *Streptococcus pneumoniae* isolates, which should provide sufficient power to allow us to estimate key antibiotic susceptibilities (objective 4), on the assumption that:

40% of UTI samples will yield a pathogen.25% of COPD samples will yield a pathogen.90% of pathogens isolated from urine will be *E. coli.*40% of pathogens isolated from sputum will be *S. pneumoniae.*In *E. coli*, resistance to nitrofurantoin, fosfomycin and co-amoxiclav will be <5% and resistance to cephalosporins and fluoroquinolones 50%–60%.^28^In *S. pneumoniae*, penicillin resistance will be 12.5% and erythromycin resistance 90%.^29^

Inclusion criteria of patients are male or female who are: (1) 18 years or older and able to give consent to participate in the microbiological study, exit survey and/or follow-up interviews; (2) presenting to the recruitment site for his/her current illness for the first time during the study period and (3) diagnosed by the attending doctor as having one or more of the following: UTI, exacerbation of COPD, upper respiratory tract infection (RTI) with productive cough and sore throat. These patients will be selected via ‘consecutive sampling’ in which, when a start date has been determined, the recruitment continues daily (7 days a week) thereafter, between 08:00 and 17:00 hours or 09:00 and 18:00 hours on alternate days, until the target numbers have been reached. All incoming patients to the site village clinics and township health centres who meet the inclusion criteria during any study day are invited to participate. This is a pragmatic approach to sampling since patient record systems do not allow the flexibility to carry out random sampling, and ongoing recruitment will ensure the most efficient use of staff and resources in this setting.

Qualitative study participants will include: (1) patients visiting the selected village clinics and township health centres during the study period; (2) customers visiting the selected retail pharmacies during the study period; (3) doctors within the clinics or health centres for treatment of RTIs/UTIs; (4) salespersons working within the selected retail pharmacies.

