### Data collection

#### Specimen collection and microbiological testing (objectives 1, 2 and 4)

The study will collect sputum, throat swab and urine specimens for pathogen identification and susceptibility testing. Sputum will be collected from RTI patients with productive cough (eg, exacerbation of COPD; throat swabs from patients with sore throat and urine from patients with UTIs. Specimen collection will be performed by the attending doctor and placed into a sterilised tube according to a standard operation protocol. The specimen tubes will be put immediately into a refrigerator and preserved at below –4℃ temporarily prior to being shipped to the Central Laboratory of Anhui Medical University (AMU). At about 12:00 and 17:30 hours each day, the samples in the refrigerator will be transferred to a portable code case filled with ice bags which is then sealed and handed over to a contracted bus company. The company is held responsible for shipping the specimens within a set time limit (within 4 hours).

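### Specimen provision for objective 1 is measured as provided versus refused, so patients who agree but cannot produce a specimen are counted in neither group and feasibility can be overstated

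*Protocol article*

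**What the plan says.** Box 1 (Study aims and objectives) sets objective 1 as the feasibility of three things: getting samples in the community, isolating pathogens and determining their susceptibilities. The section Quantitative analysis (objectives 1–4) gives three measures for it:

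- Measure 1, on provision: "ratios of patients who have provided specimens versus those who have refused and their reasons for doing so".
- Measure 2, on specimen quality, is the share of specimens that laboratory technicians judge to have been taken, kept and transported correctly.
- Measure 3, on opinion, covers how exit interviewees feel about giving a specimen, and what the doctors taking part think.

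On recruitment, the Participants section says: "All incoming patients to the site village clinics and township health centres who meet the inclusion criteria during any study day are invited to participate". The target there is to "recruit a total of 1550 patients (1000 with exacerbation of chronic obstructive pulmonary disease (COPD) and 555 with UTI". The qualifying diagnoses are "UTI, exacerbation of COPD, upper respiratory tract infection (RTI) with productive cough and sore throat".

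On collection, the section Specimen collection and microbiological testing says: "Sputum will be collected from RTI patients with productive cough (eg, exacerbation of COPD". Throat swabs come from patients with sore throat and urine from patients with UTI. The attending doctor carries out the collection.

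**The concern.** Obtaining a specimen takes two things: the patient must be willing, and must be able to produce it. Measure 1 contrasts providers with refusers, so it captures willingness. Inability has no place in it. Measure 2 has existing specimens as its denominator, and measure 3 collects attitudes. A patient who agrees and then brings up no sputum, or passes no urine at the visit, is counted in none of the three.

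This matters because the two specimen types that the patient has to produce, sputum and urine, carry the whole stated recruitment target (COPD exacerbation and UTI). Inability and unwillingness also call for different remedies, and a feasibility study is where they should be told apart. The rest of the plan would not necessarily reveal the loss. Recruitment continues until target numbers are reached, and the Abstract gives 1550 as the number of samples while Participants gives 1550 as the number of patients. If the target is counted in specimens, patients who could not produce one would be replaced without leaving a trace in the reported figures.

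**Working it through.** **The plan's own figures.** The article states no expected provision, refusal or non-production rate, so there is no provision figure to reproduce. It does state expected isolates (Participants), and these reproduce:

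- *E. coli*: 555 × 0.40 × 0.90 = 199.8 (stated 200).
- *S. pneumoniae*: 1000 × 0.25 × 0.40 = 100 (stated 100).

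The yield rates are per sample, yet they are applied to the full number of patients. The calculation thus assumes one specimen from every recruited patient, with no allowance for non-production. (The components sum to 1000 + 555 = 1555 against the stated 1550; this has no bearing here.)

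**Where each invited patient is counted under objective 1.**

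| Outcome | Measure 1 | Measure 2 | Measure 3 |
|---|---|---|---|
| Specimen provided | provided | in denominator | attitude only |
| Refused | refused | not counted | attitude only |
| Agreed, unable to produce | no category | not counted | attitude only |

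**Size of the effect.** Let r be the share of invited patients who refuse and u the share of those agreeing who cannot produce a specimen. Both are assumptions. As shares of all invited:

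- provided P = (1 − r)(1 − u)
- refused R = r
- unable U = (1 − r)u, with P + R + U = 1

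The plan's ratio P:R, expressed as a share, is P/(P + R). Over all invited the share is P. The gap is P/(P + R) − P = P × U/(P + R). It is zero when U = 0 and positive whenever U > 0 and P > 0.

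With r = 10%:

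| u | P | R | U | P/(P + R) | P/invited | Gap (points) |
|---|---|---|---|---|---|---|
| 0% | 0.900 | 0.100 | 0 | 90.0% | 90.0% | 0 |
| 5% | 0.855 | 0.100 | 0.045 | 89.5% | 85.5% | 4.0 |
| 10% | 0.810 | 0.100 | 0.090 | 89.0% | 81.0% | 8.0 |
| 20% | 0.720 | 0.100 | 0.180 | 87.8% | 72.0% | 15.8 |

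Example, u = 10%: 0.810/0.910 = 89.0%, and 89.0 − 81.0 = 8.0 points.

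Varying refusal at u = 20%: r = 5% gives 93.8% against 76.0%; r = 20% gives 76.2% against 64.0%; r = 30% gives 65.1% against 56.0%.

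In ratio form, at r = 10% and u = 20%, the plan's measure is 0.720/0.100 = 7.2 to 1. Provided against all not provided is 0.720/0.280 = 2.57 to 1.

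As u goes from 0% to 20% at 10% refusal, the plan's share moves only from 90.0% to 87.8%, while the share of invited patients yielding a specimen falls from 90.0% to 72.0%. The measure barely responds to this obstacle.

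**The case against.** **The clause may be shorthand.** It could stand for patients who gave a specimen against those who did not, with inability recorded among the reasons. A journal article also leaves log coding to the full protocol, and the log is not shown. This stands in part. A reader might infer that the study will certainly exclude non-producers and certainly overstate feasibility, and the document does not support that. But the article does state the measure, and states it with two categories. If inability were filed under refusal, the total would be right but inability would be labelled as unwillingness.

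**The exposed group is limited.** Sputum is taken from patients with productive cough, and a throat swab needs nothing produced by the patient. This stands: the point concerns mainly sputum and, less so, urine. Some exposure remains, because the inclusion criteria list COPD exacerbation without clearly attaching productive cough to it.

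**Much of the reporting chain is already planned.** Specimen quality, pathogen positivity by diagnosis and specimen type, and resistance percentages are all in the same section. This stands. What is missing is the step with no specimen and the denominator of all eligible invited patients.

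**The size has no source in the document.** This stands. Every value of r and u is assumed, and the gap is small or nil if non-production is rare.

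**The consequence is limited.** A reader might infer that this ratio decides whether routine monitoring is recommended. The article sets no threshold or go/no-go rule for it, and feasibility is judged on three measures together.

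**Conclusion.** The point holds as a defect in a stated measure. As written, patients who agree but cannot produce a specimen are in neither group, and no objective 1 measure is taken over all eligible invited patients. The direction is arithmetic: leaving out a non-empty group of non-producers can only raise the apparent provision rate. The size cannot be set from the document. At an assumed 10% refusal it runs from 0 points with no non-production to 4, 8 and about 16 points at 5%, 10% and 20% of those agreeing. These figures apply within a specimen type that the patient must produce, not to all invited patients taken together.

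A reader might also infer a shortfall in isolates from the assumption of one specimen per patient. The document does not establish one, because recruitment runs until target numbers are reached and the Abstract counts the target in samples. The conclusion is confined to how feasibility is reported: the result informs the judgement on routine monitoring and does not settle it alone.

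**What to change.** In Quantitative analysis (objectives 1–4), replace the provided-versus-refused ratio with two proportions, each by specimen type (sputum, throat swab, urine):

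- specimens obtained / all eligible patients invited for that specimen type;
- specimens acceptable on arrival at the laboratory / all eligible patients invited for that specimen type.

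Show those without a specimen as two separate counts: refused (with reasons), and agreed but unable to produce. Assign each invited patient to the specimen type or types that the presentation calls for, so that refusers and non-producers also enter the right denominator. The existing quality percentage among specimens received can stay alongside.

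The cost is one extra category on the recruitment log and a changed denominator; recruitment, specimen handling and laboratory work are unaffected. The possible downside is a less favourable figure. The category should be in place while patients are being recruited, since it may not be recoverable afterwards. If the full protocol already records it, a clarifying sentence is enough.

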**Methods and analysis:**

We will conduct direct observations, structured and semistructured interviews in retail pharmacies, village clinics and township health centres to investigate treatment-seeking and antibiotic use. Clinical isolates from 1550 sputum, throat swab and urine samples taken from consenting patients at village and township health centres will be analysed to identify bacterial pathogens and ascertain antibiotic susceptibilities. Healthcare records will be surveyed for a subsample of those recruited to the study to assess their completeness and accuracy.

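### Positivity is counted per specimen and resistance per isolate, with no stated limit of one per patient, although the text allows a patient with productive cough and sore throat to give both sputum and a throat swab

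*Protocol article*

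**What the plan says.** All references are to the protocol article.

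- **Unit for positivity** (Quantitative analysis, objectives 1–4): "percentages of pathogen positive specimens in terms of all and specific bacteria by diagnosis, type of specimen, patient-reported symptoms". The same list goes on to treatment history and sociodemographics, which are attributes of patients.
- **Unit for resistance** (same section): "calculating percentages of resistant pathogens by type of bacteria and antibiotics". This is not split by specimen type.
- **Test** (same section): a chi-square test compares "these pathogen and resistance rates in non-hospitalised patients with those from analyses of data from large urban hospitals".
- **Specimen rule** (Specimen collection and microbiological testing): "Sputum will be collected from RTI patients with productive cough", and "throat swabs from patients with sore throat and urine from patients with UTIs". The rule gives no alternative or order of priority for a patient who meets two conditions.
- **Eligibility** (Participants): the patient is "diagnosed by the attending doctor as having one or more of the following". One listed diagnosis is an upper respiratory infection described by both a productive cough and a sore throat.
- **Totals**: the Abstract plans "Clinical isolates from 1550 sputum, throat swab and urine samples taken from consenting patients". Participants plans 1550 patients, made up of 1000 with COPD exacerbation and 555 with UTI.

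**The concern.** Objective 2 (Box 1) asks for the prevalence of resistance in non-hospitalised patients and tests whether it is lower than in large urban hospitals. The analysis section uses specimens and isolates as its units. If one patient can supply two respiratory specimens, these units are not patients and are not independent of each other.

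Two things are at stake. First, a double-sampled patient enters pooled respiratory positivity twice, so breakdowns by diagnosis, symptom, treatment history or sociodemographics can lean towards the patients with both symptoms. Second, the same strain grown from sputum and from the swab becomes two resistant (or two susceptible) pathogens in the chi-square test. The test then uses too small a standard error and rejects too often when there is no difference.

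**Working it through.** **1. The plan's own forecast.** The rates in Participants give:
- E. coli: 555 × 0.40 × 0.90 = 199.8 (stated 200).
- S. pneumoniae: 1000 × 0.25 × 0.40 = 100 (stated 100).

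Both reproduce with one specimen per patient. The S. pneumoniae figure uses sputum only; throat swabs do not enter it.

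**2. Do the totals settle one specimen per patient?** The Abstract has 1550 samples and Participants has 1550 patients, which points to one each. But the patient total consists only of COPD and UTI (1000 + 555 = 1555), with no throat-swab group, while the Abstract counts swabs among the 1550 samples. Swabs must therefore come either from patients already counted for another specimen or from a group that the total omits. The article does not say which.

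**3. How the stated units count one visit.** For a patient with both symptoms and both specimens:
- The same strain in both: 2 positive specimens and 2 isolates from one infection.
- Sputum positive, swab negative: 1 of 2 specimens positive, although the patient is positive.

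**4. Effect on the test.** Let n patients carry a given species, and let a share q of them contribute a second isolate with the same result. The documents do not give q, so a range is assumed.
- Isolates counted: n(1 + q).
- Sum of squared patient weights: n(1 − q) + 4nq = n(1 + 3q).
- True variance divided by the variance the test assumes: (1 + 3q)/(1 + q).
- Actual level of a nominal 5% two-sided test, with the hospital series taken as a large fixed reference: 2[1 − Φ(1.96/√inflation)].

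With n = 100 for illustration:

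| q (assumed) | isolates counted | variance inflation | effective isolates | actual level |
|---|---|---|---|---|
| 0.10 | 110 | 1.18 | 93.1 | 7.1% |
| 0.25 | 125 | 1.40 | 89.3 | 9.8% |
| 0.50 | 150 | 1.67 | 90.0 | 12.9% |

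The protocol article states no significance level; 5% is assumed. A smaller hospital series would bring the actual level nearer to 5%, because only the community part of the variance is inflated.

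**5. If sputum and swab results are independent.** The S. pneumoniae yield per specimen is 0.25 × 0.40 = 10%; applying this to swabs is an assumption. Both specimens are positive in 0.10² = 1% of patients and at least one in 1 − 0.90² = 19%. Even if every patient gave both, q = 1/19 = 5.3%, the inflation is 1.158/1.053 = 1.10, and the level is about 6.2%.

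**6. Effect on the resistance percentage.** This moves only if double-sampled patients differ from the rest. Assume 20% resistance in them and 10% in the others:
- q = 0.10: (0.10 × 2 × 0.20 + 0.90 × 0.10)/1.10 = 11.8% per isolate, against 11.0% per patient, a shift of 0.8 points.
- q = 0.50: (0.50 × 2 × 0.20 + 0.50 × 0.10)/1.50 = 16.7%, against 15.0%, a shift of 1.7 points.

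**The case against.** The strongest reply is that the article never says two specimens are taken. It matches specimen types to presentations, and the equal totals and the isolate forecast both suggest one specimen per patient. Collection follows a standard operating procedure, and a full research protocol exists; neither is shown, and a rule for repeat isolates could sit in either. This stands to the extent that double sampling is possible on the text but not established. It does not dispose of the point. The totals leave the source of the swabs unexplained, and the analysis section is not silent on the unit: it names patients when it measures specimen provision and specimens when it measures positivity, even for patient attributes.

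A reader might infer more than the documents support:
- **That the rule takes both specimens from every patient with both symptoms.** This is an inference from a rule that states no alternative.
- **That the 100 forecast S. pneumoniae isolates shrink to fewer patients.** That forecast is built on sputum alone, so duplicates from swabs would add to the 100.
- **That specimen-level positivity of 25% hides a patient-level figure of 44%** (1 − 0.75² = 43.75%). This needs independent results and the COPD yield applied to swabs. It cannot be combined with the 7% to 13% range, which needs the same strain in both specimens. With full concordance, patient-level positivity stays at 25%.
- **That every breakdown is affected.** UTI and E. coli results (200 of the 300 forecast isolates) are not touched by the sputum-plus-swab route, and the breakdown by specimen type already keeps the two apart.

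**Conclusion.** The point holds in limited form. The stated units, the symptom-based specimen rule and the eligibility text together allow one respiratory infection to be counted twice, and no stated rule prevents it. Whether it will happen depends on passages that must be reconciled: the sample total in the Abstract, the patient total in Participants, and the specimen rule.

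Where both specimens are taken, the exposed results are pooled respiratory positivity by patient attribute, and the standard errors and chi-square tests for resistance in respiratory species. The actual level of a nominal 5% test is about 7% to 13% if 10% to 50% of isolate-positive patients are counted twice with the same result, and about 6% if the two specimens behave independently. These figures rest on assumed overlap and concordance, neither of which the documents give, and on a large hospital reference series. The resistance percentages themselves need not be biased.

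**What to change.** In Quantitative analysis (objectives 1–4):
- For resistance percentages and the chi-square test, count one isolate per species per patient visit, under a rule stated in advance for when sputum and swab grow the same species (for example, keep the sputum isolate).
- For breakdowns by diagnosis, symptoms, treatment history and sociodemographics, calculate respiratory positivity per patient, positive if any specimen is positive.
- Keep per-specimen percentages only for type of specimen.
- Report the numbers of patients and of specimens separately.

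Reconcile the Abstract, Participants and specimen collection sections so that they state whether a patient can give more than one specimen, and which patients supply the throat swabs within the 1550.

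The cost is analysis wording; no new data are needed. The reported isolate count falls by the number of within-visit duplicates. If each patient gives only one specimen, the results do not change.

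### Specimen type stratifies pathogen positivity but not resistance or the hospital comparison, so specimen mix can enter the objective 2 test

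*Protocol article*

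**What the plan says.** The Quantitative analysis section of the protocol article sets out objective 2 in three steps.

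- Item (1) covers positivity: "estimating percentages of pathogen positive specimens in terms of all and specific bacteria by diagnosis, type of specimen, patient-reported symptoms", followed by treatment history and sociodemographics.
- Item (2) covers resistance: "calculating percentages of resistant pathogens by type of bacteria and antibiotics".
- Item (3) compares, by χ² test, "these pathogen and resistance rates in non-hospitalised patients with those from analyses of data from large urban hospitals".

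The section on specimen collection and microbiological testing says that sputum comes from patients with productive cough, with "throat swabs from patients with sore throat and urine from patients with UTIs". All three specimen types go to identification and susceptibility testing. Sputum and throat swabs are cultured on the same four plates. The comparison data come from existing diagnostic laboratory databases, and no restriction by specimen is stated.

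The Participants section forecasts 100 *S. pneumoniae* and 200 *E. coli* isolates. The forecast uses yields for COPD and UTI samples and the assumption that "40% of pathogens isolated from sputum will be" *S. pneumoniae*. It gives no number, yield or species mix for throat swabs.

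**The concern.** Specimen type is named as a stratum for positivity and is absent from the shorter list for resistance in the next item. Item (3) then tests the rates so defined. Followed literally, all isolates of one species share one rate per antibiotic, whichever specimen they came from.

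Objective 2 tests whether resistance is lower in the community than in large urban hospitals. If the mix of specimens differs between the two sources, and resistance differs by specimen, the χ² test can show a difference that belongs to the mix and not to the setting. It can equally hide a real one. The article's Introduction criticises existing surveillance figures because of who gets sampled, so the study's own comparison should be protected against a problem of the same kind.

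**Working it through.** **1. The plan's own isolate forecast (Participants section).** Expected isolates = patients × yield × species share.

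- *S. pneumoniae*: 1000 × 0.25 × 0.40 = 100.0 (stated 100).
- *E. coli*: 555 × 0.40 × 0.90 = 199.8 (stated 200).

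Both reproduce. The first uses COPD samples and sputum only, the second urine only. The two patient groups sum to 1000 + 555 = 1555, which already exceeds the stated total of 1550. No part of the target is therefore assigned to throat swabs, although the Abstract counts them among the 1550 samples and patients with upper respiratory infection are eligible.

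**2. The strata side by side.**

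| Step | Stated strata | Specimen type named? |
|---|---|---|
| (1) Positivity | bacterium, diagnosis, specimen, symptoms, prior treatment, sociodemographics | yes |
| (2) Resistance | bacterium, antibiotic | no |
| (3) χ² against hospitals | the rates from (1) and (2) | no match stated for resistance |

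**3. Which species are exposed.** Only those recovered from more than one specimen type. *S. pneumoniae* is the main case, since sputum and throat swabs are worked up identically. The four respiratory plates include MacConkey agar, so on a literal reading an *E. coli* from a respiratory specimen would also join the rate forecast from urine.

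**4. What mixing does.** Let *s* be the throat-swab share of the isolates, and *p*S and *p*T the resistance in sputum and throat isolates.

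- Combined rate = (1 − *s*) × *p*S + *s* × *p*T, so the shift from the sputum rate is *s* × (*p*T − *p*S).
- If resistance within each specimen type were the same in community and hospital, the combined rates would still differ by (*s*community − *s*hospital) × (*p*T − *p*S).

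The difference vanishes if the shares are equal or if resistance does not differ by specimen.

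**5. Illustration, on assumed values.** The documents give neither *s* nor *p*T. The 12.5% penicillin resistance is stated for *S. pneumoniae* in general; using it for sputum is itself an assumption.

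- *s* = 0.5, throat 10 points lower: 0.5 × 12.5% + 0.5 × 2.5% = 7.5% (shift −5.0 points).
- *s* = 0.1, throat 10 points lower: 0.9 × 12.5% + 0.1 × 2.5% = 11.5% (shift −1.0).
- *s* = 0.5, throat 5 points higher: 0.5 × 12.5% + 0.5 × 17.5% = 15.0% (shift +2.5).
- Throat equal to sputum: 12.5% for any *s* (shift 0).

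A wider assumption changes the picture: with *s* = 0.6 and throat resistance of 5% or 30%, the rate is 8.0% or 23.0%. The range follows from the assumptions and is not an estimate.

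**6. Precision.** With 100 isolates at 12.5%, the 95% half-width is 1.96 × √(0.125 × 0.875 / 100) = 6.5 points. A sputum-only estimate keeps this, because the 100 were forecast from sputum. If a total of 100 were instead made up of 75 sputum and 25 throat isolates, the half-widths would be 7.5 and 13.0 points.

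**The case against.** The article nowhere says that throat and sputum isolates will be combined. It is a condensed account, and a fuller document may hold the table strata. Rates are at least separate per species and drug. The same section also opens by promising to relate resistance rates to patient characteristics, and under objective 4 it would "explore relationships between pathogen types and susceptibilities and patient characteristics such as presenting symptoms, clinical diagnosis, prior use of antibiotics and demographics". Because specimens are taken according to symptoms, such an analysis would partly separate sputum from throat isolates.

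Part of this stands. Pooling is the plain reading of the listed strata, not a declared rule. But the article does give a list for each step, and the lists differ; this is more than silence. The objective 4 analysis does not close the gap. It is conditional ("If sample sizes allow it, descriptive analyses may be followed by analytical studies"), it does not name specimen type, and it does not feed the χ² test. Symptoms are also an imperfect stand-in for specimen, since the eligibility wording for upper respiratory infection mentions productive cough and sore throat together.

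A reader might infer more than the documents support:

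- **That throat isolates are carriage strains with different resistance.** The documents never mention carriage and give no resistance figure by specimen. The need to compare like with like does not depend on it.
- **That a bias of a known size exists.** The throat share and throat resistance are both unknown. The missing throat-swab target is as consistent with few swabs as with many.
- **That the weight of COPD patients puts the sample outside the mild to moderate infections discussed in the Introduction.** Nothing shows that COPD patients seen at village clinics and township centres fall outside that description.

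**Conclusion.** The point holds as a gap in the analysis strata. Resistance and its hospital comparison are not stratified or matched by specimen, whereas positivity is, so specimen mix can confound the objective 2 test for any species found in more than one specimen type. It should be corrected, because it touches the study's one stated comparative hypothesis and is cheap to settle before the data are seen.

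It is not a demonstrated bias. Neither size nor direction can be computed from the documents, and the shifts of −5.0 to +2.5 points rest wholly on assumed shares and resistance differences. No figure stated in the plan is wrong on this account, and the isolate forecasts reproduce.

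**What to change.** - **Objective 2, item (2):** calculate resistance by bacterium, antibiotic and specimen type. Item (1) already needs specimen type, so nothing new has to be collected.
- **Objective 2, item (3):** compare like with like. Use sputum isolates for the main *S. pneumoniae* comparison and urine isolates for *E. coli*, each against hospital isolates of the same specimen type where the laboratory databases record it. Report throat-swab isolates separately.
- **If the databases do not record specimen type:** state that the comparison is unmatched and interpret it as such.

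The cost is a change of wording, more table rows and smaller strata. The matched comparison also depends on a specimen field in the hospital data, which the documents do not confirm. The planned numbers of sputum and urine isolates (100 and 200) do not change.
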